#### Prognostic measures

The demand-control-support model [39] will be considered as a possible prognostic measure in this study. The study will also include items from the General Nordic Questionnaire (QPSNordic) relating to ongoing conflicts with the superior, perceived loss of control over work tasks and conflicts between the employee’s values and how the work is actually carried out [40]. One self-efficacy item about how confident participants are about whether they will be back to their usual working hours in their usual work position 3 months after the baseline measurement will be developed and validated within the project. Finally, the OHS consultants will be asked a similar question about whether the employee will be back to his/her usual working hours in 3 months’ time.

### Cost-effectiveness

A full economic evaluation of costs for society and for the employer will be conducted [41]. The expenses that will be collected are direct costs, such as intervention costs paid by the employer and possible rehabilitation provided by other caregivers. Indirect costs such as time used by participants for the intervention and travel time will also be collected. Time for the intervention will be calculated on the basis of the intervention program. Time for travel to attend the meetings will be standardized at 1 h per meeting (30 min/single way). Treatment costs will be estimated using national unit costs and the fee charged by the OHS. Lost time due to treatment or travel will be evaluated using national median wages. Information about absenteeism and reduced performance due to health-related and work environment-related problems, i.e. productivity loss, will be collected using validated questions and used to calculate potential benefits of the intervention. Productivity loss will be estimated using national median wages.

Data regarding the direct costs and potential savings which emerge from the intervention will be collected in parallel with the implementation of the project and for a 1-year follow-up period. All costs and consequences will be converted to a single year using the consumer price index. Discount of costs or consequences is not needed for the 1 year follow-up because of the short follow-up period. Costs or savings that occur during the long term follow-up will be discounted using a 3 % discount rate [42]. The employer’s economic evaluation will be conducted using a cost benefit analysis; the evaluation of the economic costs for society will be conducted using a cost effectiveness analysis.

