### Primary outcome

#### Registered sickness absenteeism

The primary outcome is the total number of days of sickness absence during the 12-month follow-up period (including sickness benefit and disability pension). Sickness benefit and disability pension will also be analyzed separately.

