#### Statistical power

Sample sizes of 75 in Group 1 and 75 in Group 2, which were obtained by sampling 15 clusters with an average of five subjects each in Group 1 and 15 clusters with an average of five subjects each in Group 2, achieve 84% power to detect a difference between the group means of at least 25.00 days of registered sickness absence 1 year after baseline. The standard deviation of subjects is 50.00. The intra-cluster correlation coefficient is 0.010. The coefficient of variation of cluster sizes is 0.650. A two-sided t-test was used with a significance level of 0.050. This test used degrees of freedom based on the number of subjects. No missing values are expected since the primary outcome is based on register data. The aim of the current study is therefore to include a total of 150 participants.

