### Methodological considerations

We cannot exclude the risk of selection bias i.e. that the OHS consultants choose which employees to invite to participate in the study on the basis of, for example, how well they believe the intervention would work for a particular employee. Hence, during the training and follow-ups with the OHS consultants, we emphasize the importance of telling all employees who match the inclusion criteria about the study. We will also include an item relating to this in the process evaluation check-lists that will be distributed to the OHS consultants.

There is also risk of possible contamination of interventions because OHS consultants at the same OHS may deliver either care as usual or the experimental intervention. This concern is, similarly to the above, addressed in the training and follow-ups of the OHS consultants belonging to the intervention group, at which the reasons for not discussing the intervention contents with colleagues allocated to deliver the control condition are explained. An item on this issue will also be included in the process evaluation check-list to the OHS consultants.

In Sweden, the employer records and pays for sick leave related costs up to and including the 14th day of sick leave. For this reason, national, register-based data on sick leave maintained by the SSIA is available from the 15th day onwards, with no information available for short-term sick leave. The current study consequently sends text messages that include questions about short-term sick leave (< 15 days) to all participants once every 4 weeks. This will give valuable information about short-term sick leave among the participants. Nevertheless, the reliance on similar self-reports is subject to possible recall bias and larger drop-out rates than register-based data. To increase the response rates, we have used reminders by calling employees about missing answers; in a previous study this was found to increase response rates [45].

Two previous Swedish studies have shown that employees with CMDs may seek treatment on their own, especially if they are aware that they belong to the control group [46, 47]. To detect possible treatment bias of this sort, items on co-interventions have been included in the questionnaires to the employees. The OHS consultants have also been advised not to inform employees whether they belong to the control or the intervention group, since active workplace-focused treatments are given in both conditions.

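### The economic evaluation names only self-report as its source of absence days, although register days from day 15 of a spell are held for every participant

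*Protocol article*

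**What the plan says.** The Cost-effectiveness section gives a source for most of its components. Intervention time comes from the programme, travel is set at 1 h per meeting, treatment is priced from national unit costs and the OHS fee, and lost time is valued at national median wages. For absence it says that information on absenteeism and reduced performance, which it equates with productivity loss, "will be collected using validated questions and used to calculate potential benefits of the intervention". The SSIA register is not mentioned in that section.

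Elsewhere the article describes the absence data as follows.

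- **Primary outcome, Registered sickness absenteeism:** total registered days over 12 months, counting sickness benefit and disability pension.
- **Statistical power:** "No missing values are expected since the primary outcome is based on register data".
- **Methodological considerations:** register data "is available from the 15th day onwards, with no information available for short-term sick leave", because "the employer records and pays for sick leave related costs up to and including the 14th day of sick leave".
- **Methodological considerations, on self-reported absence:** "the reliance on similar self-reports is subject to possible recall bias and larger drop-out rates than register-based data".
- **Measurements and procedure:** the reason given for the text messages is that they also pick up spells shorter than 15 days, which the SSIA does not cover.

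On later years, the Cost-effectiveness section adds: "Costs or savings that occur during the long term follow-up will be discounted using a 3 % discount rate". The text messages run for one year and the questionnaires end at 12 months. The only sick-leave data planned after that come from the register.

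**The concern.** For absence from day 15 onward the trial has two possible sources, and the economic section names the one that the article itself regards as weaker. The stated reason for collecting self-reported absence by text message is narrower: it fills the gap below 15 days. No reason is given for using questions on the part of a spell that the register already covers.

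What is at stake is the saving claimed for the employer (cost benefit analysis) and for society (cost effectiveness analysis). The primary effect comes from a source with a value for every participant. If the longer spells are priced from questions, the saving attached to them could also reflect who answered and what they remembered. The inclusion criteria admit employees with up to 3 months of sick leave at the first OHS visit, so long spells are to be expected. The power calculation is also framed in registered days, so the effect the trial is designed to detect lies in the days the register holds.

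**Working it through.** **1. The plan's own figure.** Inputs from Statistical power: 15 clusters of average size 5 per arm (75 per arm), difference 25 days, SD 50, ICC 0.010, coefficient of variation of cluster size 0.650, two-sided 5% test, degrees of freedom from subjects (148).

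- Design effect = 1 + ((0.650² + 1) × 5 − 1) × 0.010 = 1.061.
- Standard error = 50 × √(2 × 1.061 / 75) = 8.41 days.
- Non-centrality = 25 / 8.41 = 2.97, which gives power of 83.97%.

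The stated 84% reproduces. It concerns registered days and is not in dispute.

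**2. What the register holds.** Under the day-15 rule, register days = max(0, spell length − 14).

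| Spell (days) | Register days | Share held | Share missed |
|---|---|---|---|
| 14 or fewer | 0 | 0% | 100% |
| 20 | 6 | 30% | 70% |
| 30 | 16 | 53% | 47% |
| 60 | 46 | 77% | 23% |
| 90 | 76 | 84% | 16% |

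The register therefore cannot replace self-report for short spells or for the start of any spell. It does hold most of a long one.

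**3. What self-report could cost on the day-15-plus part.** The article gives no drop-out rate, so this step rests on assumptions. If a proportion p of an arm does not respond, and non-responders have g more days than responders, the responder mean lies below the arm's true mean by p × g. With the same g in both arms, the difference between arms shifts by (difference in p) × g.

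- Difference in p = 0.10, g = 25 days (half the stated SD): 0.10 × 25 = 2.5 days, or 10% of 25.
- Difference in p = 0.10, g = 50 days (one SD): 0.10 × 50 = 5 days, or 20% of 25.
- Equal non-response and equal g: no shift.

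A true saving of 25 days would appear as 27.5 to 30 if the intervention arm responded less, and as 22.5 to 20 if the control arm did. Precision also falls. Ignoring clustering, the standard error grows by 1/√(1 − r): 1.118 at r = 0.20 and 1.240 at r = 0.35, both rates assumed. With register days, the non-response part of this error is absent from day 15 on.

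**The case against.** The best defence is that self-report is needed here. The register has no employer-paid days, and an employer's cost benefit analysis without them would miss what the employer pays directly. Reduced performance, named in the same sentence, cannot come from any register. Part of the study population is not on sick leave at baseline, so short spells matter. Using one instrument for all absence also avoids splitting spells at day 15, and the article does not show that text messages every fourth week supply the spell start dates that a split needs. All of this stands. It is an argument for keeping self-report where the register is blank, not for using it where the register has data.

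Four stronger readings are tempting and are not supported.

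- **That a complete register count is being ignored.** The absence of missing values means every participant has a register value, not that every absence day is recorded.
- **That the economic analysis excludes register days or is confined to responders.** The section says neither. The article plans intention-to-treat analyses and describes reminder calls, and the handling of missing cost data may be set out elsewhere. Likewise, a change of source after 12 months follows only if year 1 is assumed to use self-report alone.
- **That any gap between the economic and primary totals is a contradiction.** The totals cover different days, so some difference is legitimate. Nor do the figures show a reversal of direction: a 5-day shift does not overturn a 25-day difference.
- **That long spells make up most of the absence cost.** The article gives no distribution of spell lengths or costs.

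**Conclusion.** The point holds as a worthwhile, inexpensive improvement. The article makes a positive statement about where absence data for the productivity-loss estimate come from, and it names only questions. It does not link them to the register days already obtained from day 15, and its own discussion rates self-report as the weaker source. The monetary value of longer spells could therefore carry non-response and recall error that the primary outcome avoids.

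The size is unknown. The 2.5 to 5 days is an illustration that depends on an assumed 10-point difference in non-response, an assumed gap of 25 to 50 days that is equal in both arms, and no correction for missing answers. Recall error would come on top and cannot be sized from the article. The primary outcome and the 84% power are unaffected.

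**What to change.** In the Cost-effectiveness section, replace the single source for absence with a statement along these lines:

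> Absence from day 15 of a spell is costed from SSIA register days for all included participants. Questionnaires and text messages supply days 1 to 14 of each spell, spells shorter than 15 days, and reduced performance at work. A joining rule, fixed before the data are examined, determines which source counts where the two overlap or disagree, so that no day is counted twice. A version based wholly on self-report is reported as a sensitivity analysis.

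This also puts any costing beyond 12 months on the same source from day 15 as the first year.

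The cost is a change of wording, a linkage step on data already being obtained, and the work of writing the joining rule. That rule is the real downside, because it must say how a spell is split when the text messages give no clear start date. No sample size, outcome or other stated design figure changes.

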### Process evaluation

The importance of a process evaluation for studies conducted within the OHS has been highlighted in previous research [43]. The current study will perform a process evaluation of both the OHS and the employee [44]. The purpose of this is to examine: the attitudes of the OHS consultants towards the study; the organizational support for the study (on the part of the OHS-consultants); the content of the control condition and the fidelity of the OHS-consultants to the experimental condition.

The participating OHS consultants´ attitudes towards and knowledge of the research project will be evaluated using a short questionnaire at the start of the study. Examples of items are “To what degree do you feel it is good to be part of the project?” or “To what degree do you understand the aim of the project?”

The OHS consultants in the experimental condition will be asked to rate their overall fidelity to the method for each employee during the study (this is done directly after the joint meeting with the supervisor and the employee). Telephone follow-ups with each participating consultant are conducted (both for the experimental and the control group) during the recruitment (and intervention) process. These follow-ups include questions about recruitment, such as clarifications of the inclusion criteria, as well as logistical or contextual factors related to recruitment. For the consultants delivering the experimental condition, issues concerning the feasibility of the intervention and the fidelity of the OHS consultant are examined. The meetings are summarized in short notes.

After the recruitment period is finished, fidelity to the intervention among the OHS consultants delivering the experimental intervention will be assessed by means of check-lists that will be built around key aspects of the intervention. Examples of such variables are whether contact with the workplace has been maintained and whether employees have been active in the problem-solving process and the planning of future measures. The content and fulfillment of the recommended follow-ups with employees and supervisors will also be addressed. The OHS consultants in the control condition will be given a check list where they are asked to describe the content of the characteristics of the control condition (intervention).

For all OHS consultants in the experimental and the control condition, the check lists will also include questions about the recruitment process (for instance, whether all employees who should be informed about the study actually received this information). Furthermore, organizational-level variables will be addressed, such as how the research project was introduced to the OHS consultants by the management at the OHS and how the study was supported while it was in operation.

Employee satisfaction with the intervention or treatment as usual will be assessed 6 months after the completed intervention. The assessment will consider aspects such as the quality of communication with OHS personnel, the relevance of the intervention, problem-solving skills learned during the intervention, planned adjustments at work, influence on the planned adjustments, agreement with the supervisor, the implementation of planned adjustments, whether follow-up contacts with the OHS were held, and questions about treatment satisfaction.

### Data analysis

Statistical methods adapted for cluster randomized designs will be applied. The plan is to apply various forms of regression models and mixed models. Intention-to-treat analyses will be carried out. Where relevant, per-protocol analyses will also be performed. If it appears that potential confounders have been unevenly distributed and can be expected to affect the results when the two interventions are compared, these factors will be adjusted for in the analyses. Possible interaction effects on the outcome for (1) gender x treatment (intervention) and (2) sick leave status (sick leave/no sick leave) x treatment will be checked for. If they are statistically significant, subgroup analyses will be considered.

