### Inclusion criteria

Inclusion criteria are met by employees fulfilling the following criteria:The employee seeks help at the OHS for occupational stress affecting their ability to work. If the employee is on sick leave due to adjustment disorders, anxiety or depression, the period of sick leave should not have exceeded 3 months at the time of the first OHS visit.The employee should accept involvement of the supervisor in the intervention.The employee also needs to understand both written and spoken Swedish as the study questionnaires and text messages are in Swedish.

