The study population will consist of employees with reported stress-related symptoms but no sick leave at baseline and employees on sick leave due to CMDs. As mentioned earlier, possible differential effects of the intervention in these groups may arise. Potential interactions between sick leave status at baseline and the secondary outcomes will therefore be taken into account.

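### The rule of adjusting only for factors that look uneven can leave baseline sick leave, a likely strong predictor of the primary outcome, out of the primary model

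*Protocol article*

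**What the plan says.** The Data analysis section of the protocol article sets the rule for covariates: "If it appears that potential confounders have been unevenly distributed and can be expected to affect the results when the two interventions are compared", then "these factors will be adjusted for in the analyses". Both conditions must hold. The section names no factor and gives no criterion for unevenness.

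The same section gives baseline sick leave one role: an interaction with "sick leave status (sick leave/no sick leave) x treatment will be checked for". Under Randomization, the stratification factors are OHS unit and occupational category, so sick leave is not balanced by design.

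Other sections bear on this:

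- **Outcome** (Primary outcome): "The primary outcome is the total number of days of sickness absence during the 12-month follow-up period".
- **Population** (Methodological considerations): "employees with reported stress-related symptoms but no sick leave at baseline and employees on sick leave due to CMDs". For the sick-listed, Inclusion criteria add that "the period of sick leave should not have exceeded 3 months at the time of the first OHS visit".
- **Recruitment** (Recruitment of participants; Blinding): consultants are randomised first, know their arm, and then identify and approach employees.
- **Selection** (Methodological considerations): "We cannot exclude the risk of selection bias i.e. that the OHS consultants choose which employees to invite to participate in the study". The remedies given are emphasis in training and follow-up, and a check-list item. None is analytic.
- **Matched control group**: the register comparison group is matched on diagnosis, age, sex and sick leave in the preceding 3 months.

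**The concern.** A rule that waits for visible imbalance is weak in any trial, because a strong predictor earns its place in the model whether or not the arms differ on it. Here there are two further reasons for concern.

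First, imbalance need not be chance. Clusters are randomised, but individuals enter afterwards through someone who knows the arm. A modest systematic difference in the share already sick-listed is easy to overlook with 75 per arm, and it would carry straight into an unadjusted comparison of sickness absence days.

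Second, the sample mixes people who start with no sick leave and people already absent for up to 3 months. The article does not call baseline sick leave the main prognostic factor. That it is strongly prognostic is inferred from the outcome, the mixed population, the matching on prior sick leave and the interaction check.

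At stake are part of the bias in the primary estimate, precision that available data could supply, and a primary model whose content is settled only after the data are seen.

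**Working it through.** **Inputs from the article (Statistical power):** 75 per arm, 15 clusters per arm of mean size 5, difference 25 days, SD 50, ICC 0.010, CV of cluster size 0.650, two-sided 5% t-test, degrees of freedom based on subjects (148).

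**The planned power reproduces.**
- Design effect = 1 + ((1 + 0.65²) × 5 − 1) × 0.010 = 1.061.
- SE = 50 × √(2 × 1.061 / 75) = 8.41 days.
- Noncentral t with 148 df gives 83.97%, against the stated 84%. This is the power of an unadjusted comparison.

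**Size of a possible bias.** Assume half the participants are sick-listed at baseline, and let D be the difference in mean 12-month days between sick-listed and other employees.
- Variance due to sick-leave status is 0.5 × 0.5 × D² = 0.25 D², so its correlation with the outcome is r = 0.5 D / 50 = D / 100.
- With r assumed at 0.4 to 0.6, D is 40 to 60 days. D cannot exceed 100 under the planned SD.
- Take 33/75 versus 42/75 sick-listed (44% v 56%). z = 0.12 / √(0.5 × 0.5 × 2 / 75) = 0.12 / 0.0816 = 1.47, so p = 0.14.
- Shift in the unadjusted difference = 0.12 × 40 = 4.8 days to 0.12 × 60 = 7.2 days. Against 25 days, that is 19% to 29%.

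**How often an imbalance would be noticed.** The article gives no trigger, so a 5% test serves only as an illustration. With 75 per arm around 50%, it flags a true 10-point gap in 23% of trials and a 15-point gap in 45%.

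**Simulation of the rule.** 8000 trials per setting, D = 50 (R² = 0.25), clustering ignored, adjustment triggered at p < 0.05. In the systematic-gap rows the intervention arm has 10 points more sick-listed.

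| Setting | Never adjust | Adjust if p < 0.05 | Always adjust |
|---|---|---|---|
| 10-point gap: mean bias (days) | 5.0 | 2.5–2.6 | about 0 |
| 10-point gap, no true effect: false positives | 9.3% | 5.3% | 5.0% |
| 10-point gap, true 25-day reduction: power | 68% | 80% | 93% |
| No systematic gap: empirical SE (days) | 8.2 | 7.8 | 7.1 |
| No systematic gap: power | 86% | 87% | 94% |

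**Precision on the article's own power basis.** Residual SD = 50 × √(1 − R²), with the same design effect and 148 df; R² is assumed.

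| R² | SE (days) | Power |
|---|---|---|
| 0 | 8.41 | 84.0% |
| 0.1 | 7.98 | 87.6% |
| 0.2 | 7.52 | 91.0% |
| 0.3 | 7.04 | 94.2% |
| 0.4 | 6.51 | 96.8% |

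The range r = 0.4 to 0.6 used for the bias corresponds to R² = 0.16 to 0.36, which lies inside this table.

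**The case against.** The strongest replies are these.

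- **The rule is a judgement, not a test.** It has a second condition, an expected effect on the results, and investigators who already single out sick leave might well act on a 44% v 56% split. This stands in part: the p-value trigger is an assumption, and even that trigger halves the bias in the simulation and holds false positives near 5%. But both conditions must be met, so a strong predictor that does not look uneven is still left out.
- **Analysts are masked to allocation** (Blinding). This limits steering the choice towards a favoured arm. It restores neither lost precision nor an adjustment that was never triggered.
- **Sick leave enters the interaction check.** Such a model would ordinarily contain its main effect, but the check is not the primary estimate, and Methodological considerations links it to the secondary outcomes.
- **An article may leave the covariate list to the analysis plan.** That would answer an omission. Here a rule is stated, and a plan that fixed the covariates would replace it.
- **Adjustment cures only measured selection.** This stands. Selection on how well a consultant expects the intervention to work may be largely unmeasured.

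A reader might be tempted by stronger claims that the article does not support:

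- A gap of 80 or 120 days, and so a larger bias. With half sick-listed, 80 days implies r = 80/100 = 0.8, and 120 days would need more variance (0.25 × 120² = 3600) than the planned 50² = 2500.
- That the rule will admit the consultant's own forecast, for which "the OHS consultants will be asked a similar question about whether the employee will be back to his/her usual working hours". The article lists it as a prognostic measure but neither says it will be a covariate nor states when it is collected.
- That the power calculation is wrong. The 84% reproduces for the unadjusted test described.

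**Conclusion.** The point holds as a badly fixed rule. Baseline sick leave is neither a stratification factor nor a fixed covariate, and the stated rule allows the primary model to omit it.

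The bias is possible, not certain, and its direction is unknown. Under the stated assumptions (half sick-listed, r of 0.4 to 0.6, planned SD of 50) an easily overlooked 12-point gap shifts the unadjusted estimate by 4.8 to 7.2 days. That is below one standard error (8.41 days) but a material share of the 25-day target. The precision argument needs no imbalance at all: for an assumed R² of 0.1 to 0.4 the SE falls from 8.41 to between 7.98 and 6.51 days. The article gives neither the share sick-listed nor the strength of the association, so these figures are illustrations and not estimates. The trial is not invalid without adjustment; it forgoes a cheap protection in a design that needs it.

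**What to change.** Replace the conditional rule with a covariate set fixed before outcome data are analysed and kept in the primary model whatever the observed balance:

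- sick-leave status and SSIA-registered days before the first OHS visit, for example over the previous 3 months, the window already used for the matched control group;
- age and sex;
- the stratification factors, where the number of clusters allows.

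Report the unadjusted result as a sensitivity analysis.

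Taking sick leave from before the first visit keeps it free of the consultant's influence. A blanket bar on everything recorded after treatment contact is not needed and would be awkward: under Recruitment of participants, the baseline questionnaire itself follows the consultant's first contact. The source of sick-leave status should be named, because the SSIA register begins only at day 15 of a spell (Methodological considerations) and would miss shorter ones.

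The cost is a change of wording, a slightly longer register extract and a few degrees of freedom. The stratification factors need most care. With 30 consultants there are 30 − 2 = 28 cluster-level degrees of freedom; three OHSs and the six listed occupational groups would use 2 + 5 = 7 of them, and more if units within an OHS are counted separately. Small categories may have to be merged.
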